### Participants

#### Inclusion criteria

Participants will be eligible for inclusion if they meet all of the following criteria:

diagnosed with idiopathic PD according to the Movement Disorder Society Clinical Diagnostic Criteria for PD (2015) (28), with stable physical condition;male or female, aged 40 and 80 years;Hoehn and Yahr stage 1.0 to 2.5, meeting the definition of early-stage PD (29);disease duration ≤3 years (30, 31), with a stable dosage of antiparkinsonian medications for at least 3 months before enrollment and expected to remain stable throughout the intervention and follow-up period (minimum 6 months);voluntary participation with signed informed consent;demonstrates good compliance and can complete the 12-week intervention and 1-year follow-up, including all planned study visits.

#### Exclusion criteria

Participants will be excluded if they meet any of the following criteria:

atypical or secondary parkinsonism, or any serious cardiovascular, cerebrovascular, hepatic, renal (creatinine clearance < 30 mL/min), hematologic, oncologic, or other neurological disorders (e.g., stroke and epilepsy);diagnosis of severe psychiatric disorders (e.g., schizophrenia and major depressive disorder), or evidence of cognitive, hearing, or visual impairment that may interfere with assessments (MoCA < 26, ranging from 0 to 30, with a score of 26 or higher indicating normal cognitive function) (32);untreated or uncontrolled physical pain that may affect gait, such as severe osteoarthritis or lumbar disc herniation;use of medications affecting motor or neurological function (e.g., antipsychotics, anticholinergics, and benzodiazepines) within 30 days prior to enrollment, except for stable-dose antiparkinsonian drugs;participation in another clinical trial within 30 days before screening;presence of skin diseases affecting acupuncture sites, such as psoriasis or local infections;history of allergic reactions to acupuncture or severe needle phobia.

Participants may withdraw at any time due to treatment intolerance, adverse events (AEs), or personal preference. Participants who experience serious AEs or become non-compliant will be advised to discontinue, and the reason and timing will be documented in the case report forms (CRFs). Outcome assessments will be sought from withdrawn participants whenever possible.

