### Concomitant treatments

Participants who have been on stable antiparkinsonian medication regimens (dopamine agonists, levodopa, or MAO-B inhibitors, alone or in combination) for at least 3 months prior to enrollment will maintain their medication throughout the 12-week intervention and 1-year follow-up unless clinical indications necessitate adjustments (36). The use of additional antiparkinsonian or central nervous system agents is prohibited; any deviations will be documented and accounted for in statistical analysis. Medications for comorbid conditions (e.g., hypertension and diabetes) are permitted and will be documented at each visit. In case of symptom worsening, medication adjustments may be made under physician guidance, with changes recorded in CRFs and converted to levodopa equivalent daily dose (LEDD) for analysis. Stable non-acupuncture interventions (e.g., rehabilitation or exercise) unrelated to motor function are permitted; their use will be recorded at each visit and adjusted as covariates in the mixed-effects model analysis.

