### Statistical analysis

All statistical analyses will be conducted using SPSS version 28.0 (SPSS Inc., Chicago, IL, USA). Continuous variables will be presented as means ± standard deviations (for normally distributed data) or medians with interquartile ranges (for non-normally distributed data), determined using the Shapiro–Wilk test. Categorical variables will be expressed as counts and percentages. Between-group comparisons at baseline will be performed using independent-samples *t*-tests or Mann–Whitney *U* tests for continuous variables and chi-square tests or Fisher’s exact tests for categorical variables. Baseline covariates (e.g., age, sex, disease duration, and LEDD) will be adjusted where applicable. Longitudinal changes in primary and secondary outcomes will be analyzed using a mixed-effects model for repeated measures, with fixed effects for group, time, and group-by-time interaction, and adjusting for relevant covariates. In cases where the assumption of sphericity is violated (Mauchly’s test *p* < 0.05), the Greenhouse–Geisser correction will be applied. Post-hoc multiple comparisons will be adjusted using the Bonferroni method; sensitivity analyses will also be conducted using either unadjusted comparisons or the false discovery rate (FDR) approach. Primary analyses will follow the intention-to-treat (ITT) principle, including all randomized participants. Missing data will be handled using multiple imputation by chained equations (MICE) (24, 43), incorporating covariates (e.g., age and LEDD); sensitivity analyses will assess robustness for the 15-month follow-up. For blinding assessment, questionnaires will be administered at months 3, 12, and 15 to calculate the Bang Blinding Index, with post-hoc sensitivity analyses addressing potential biases. A per-protocol (PP) analysis will be performed on participants who complete ≥80% of scheduled treatment sessions. Exploratory subgroup analyses will examine acupuncture effects by gender, age (<60 vs. ≥60 years), and disease duration (≤1 vs. >1 year), using interaction terms in mixed-effects models to assess heterogeneity, interpreted cautiously due to power limitations. A two-tailed *p* value of < 0.05 will be considered statistically significant.

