### Data management and quality control

All research personnel will undergo standardized training on protocol procedures, including participant screening, informed consent acquisition, CRF completion, and outcome assessments. Paper-based documents will be securely stored in locked filing cabinets, while electronic data will be maintained in encrypted, password-protected databases. Data monitoring will be conducted by the Clinical Research Center of Chengdu University of Traditional Chinese Medicine. An independent data monitoring committee will regularly review accumulated safety data, assess protocol adherence, and make recommendations regarding study continuation. Routine audits may be conducted by the ethics committee to ensure regulatory compliance. All records will be archived for a minimum of 5 years following study publication. Any protocol deviations or violations will be documented and reported to the ethics committee for evaluation and corrective action. To promote adherence, participants will use a digital app (e.g., WeChat-based reminders) for appointment tracking, with >80% completion required for per-protocol analysis; non-compliance will be mitigated through flexible scheduling and transportation support. For follow-up assessments, monthly phone reminders and incentives (e.g., travel reimbursement) will reduce attrition, with core outcomes (CCMS and PDQ-39) evaluated at all time points (baseline to month 15). Support includes transportation reimbursement, flexible scheduling, and a dedicated coordinator to address side effects or adherence issues, ensuring ethical transparency and participant wellbeing. AEs will be monitored at all visits (baseline to month 15), with delayed events (e.g., post-treatment fatigue) tracked via monthly phone follow-ups. SAEs will be reported to the ethics committee within 24 h for comprehensive long-term safety assessment.

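### Advising non-compliant participants to discontinue has no stated purpose and may add avoidable treatment loss and some adherence-related missing week-12 data to the ITT analysis (minor)

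*Protocol article*

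**What the plan says.** All references are to the Protocol article.

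- **Exclusion criteria, closing paragraph.** "Participants who experience serious AEs or become non-compliant will be advised to discontinue", with the reason and timing recorded. The next sentence reads: "Outcome assessments will be sought from withdrawn participants whenever possible". Non-compliance is not defined here, and the text does not say whether discontinuing means stopping sessions or leaving the study.
- **Inclusion criteria.** Expected adherence is screened before entry: a participant "demonstrates good compliance and can complete the 12-week intervention and 1-year follow-up, including all planned study visits".
- **Statistical analysis.** "Primary analyses will follow the intention-to-treat (ITT) principle, including all randomized participants". Missing data are handled by multiple imputation by chained equations (MICE). Attendance is dealt with separately: "A per-protocol (PP) analysis will be performed on participants who complete ≥80% of scheduled treatment sessions".
- **Data management and quality control.** "non-compliance will be mitigated through flexible scheduling and transportation support". The same section adds phone reminders and incentives, and has the CCMS evaluated at every time point to month 15.
- **Safety assessments** and the limitations in the **Discussion** also answer adherence difficulty with counselling, flexible appointments and help with travel.

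**The concern.** The sentence joins two triggers that call for different responses. A serious adverse event can be a reason to stop needling. Missing sessions is not a hazard that stopping would remove.

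Once a person is randomized, an ITT analysis needs that person's week-12 CCMS whatever the attendance. Advising a poor attender to stop can do two things, neither of them useful. It can turn partial treatment into none. It can also make the person less likely to come to week 12, and to weeks 38 and 64, where CCMS change to week 64 is a secondary outcome. The missing values would then depend on adherence. If imputation fills them with values typical of those who kept attending, the ITT estimate drifts slightly towards the effect in attenders.

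The situation is foreseeable: the article's own limitations name the load of 36 sessions in 12 weeks as an adherence challenge.

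**Working it through.** **1. The plan's own figures.** Inputs from Sample size calculation: difference 6.91, SD 8.56, two-sided alpha 0.05, power 90%, dropout 20%, then a 20% increase for centres.

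- Exact two-sample t-test: 33.24, rounded up to 34 per group.
- Dropout: 34 / (1 − 0.20) = 42.5, rounded up to 43.
- Centres: 43 × 1.2 = 51.6, rounded up to 52 per group.

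The chain 34, 43, 52 reproduces.

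**2. Is power at stake?** With 52 per group and the same effect size, exact t-test power is 0.953 at 20% missing, 0.941 at 25%, 0.925 at 30% and 0.905 at 35%. The 34 evaluable per group are reached only at 1 − 34/52 = 34.6% missing. The rates above 20% are assumptions. A few extra missing values hardly move power, so what remains on the missing-data side is bias.

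**3. Size of the bias, by illustration.** The document gives no rate of non-compliance, so all four inputs are assumed:

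- p: fraction of the true acupuncture arm that becomes non-compliant;
- dq: extra fraction of these with no week-12 CCMS because of the advice (not all missingness among them);
- r: fraction of the treatment effect that they keep;
- m: fraction of their shortfall that imputation fails to recover from earlier visits.

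With complete data the ITT effect is the full effect times 1 − p(1 − r). The unrecovered shortfall adds p × dq × m × (1 − r). So:

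overstatement = p × dq × m × (1 − r) / [1 − p(1 − r)]

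| Scenario (r = 0.5) | p = 5% | p = 10% | p = 20% |
|---|---|---|---|
| dq = 0.10, m = 0.5 | 0.00125/0.975 = 0.13% | 0.0025/0.95 = 0.26% | 0.005/0.90 = 0.56% |
| dq = 0.25, m = 1 | 0.00625/0.975 = 0.64% | 0.0125/0.95 = 1.32% | 0.025/0.90 = 2.78% |
| dq = 0 | 0% | 0% | 0% |

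**4. Extra missing values per arm** = n × p × dq. With 52 per arm (Sample size calculation): 52 × 0.05 × 0.10 = 0.26. With 60 per arm (Abstract): 60 × 0.20 × 0.25 = 3.0.

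**5. The passages side by side.** Statistical analysis needs outcomes from everyone randomized and has a separate set for low attendance. Safety assessments, Data management and quality control, and the Discussion all try to keep poor attenders in treatment. Only the withdrawal paragraph advises them to stop.

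**The case against.** The best defence is in the same paragraph. Its next sentence already seeks outcomes from those who stop, the retention measures cover CCMS at all time points, 20% dropout is planned for, and imputation could draw on the CCMS scheduled at weeks 4 and 8. The rule is advice, not removal, and discontinuing can be read as stopping sessions while assessments go on. All of this stands, and it is why the effect is probably small. It does not remove the point: seeking outcomes where possible is weaker than keeping people on the visit schedule, and the word withdrawn points towards leaving.

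A second defence is that a condensed article may leave the definition of non-compliance, and the reason for the rule, to the full protocol. That is fair, and the missing definition is not counted here. The advice itself is a stated conduct rule, and sites that follow it as written will act on it.

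A reader might go further than the document allows in four ways:

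- **A strict contradiction with the support measures.** Not shown. Support first, with advice to stop only if support fails, is a consistent reading.
- **A contrast with prohibited-drug deviations being exempt from discontinuation.** Concomitant treatments says only that "any deviations will be documented and accounted for in statistical analysis". It does not say that such participants are not advised to stop.
- **A conflict between the per-protocol cut-offs.** Statistical analysis uses at least 80%, while Data management and quality control has ">80% completion required for per-protocol analysis". With 36 sessions, 28/36 = 77.8% and 29/36 = 80.6%, so both mean 29 or more.
- **A biased or underpowered primary analysis.** Steps 2 and 3 do not support this.

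**Conclusion.** The point holds as a cheap improvement of minor weight. The non-compliance half of the rule serves no purpose that the plan states or its analyses need, and it can only add avoidable treatment loss and some adherence-related missing data. It is not a demonstrated error in the primary analysis.

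The size cannot be computed from the document. The illustration runs from zero to 2.8%. The upper end needs 20% non-compliance, a quarter of those people lost because of the advice, and imputation that recovers nothing. The direction assumes that non-compliers in the true acupuncture arm keep less of the effect and that non-compliance under sham has no matching consequence. Loss of treatment works the other way, by shrinking the effect that ITT measures, and it cannot be sized from the document either.

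**What to change.** In the closing paragraph of Exclusion criteria:

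1. Delete non-compliance as a reason to advise discontinuation, and refer instead to the support measures in Safety assessments and in Data management and quality control.
2. State that discontinuation, after a serious adverse event or for any other reason, means stopping acupuncture sessions only.
3. Replace the last sentence with: Every randomized participant stays on the week 4, 8, 12, 38 and 64 assessments unless consent to data collection is withdrawn; data collected after sessions stop are used in the ITT analysis.

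The cost is a small amendment and site retraining. No visits or patients are added. Keeping the outcomes of people who stopped sessions may make the observed effect slightly smaller.

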### Intervention

#### TA group

Participants assigned to the TA group will receive manual acupuncture using sterile disposable stainless steel needles (0.25 mm × 40 mm, Huatuo, Suzhou, China). Acupoints were selected based on prior clinical and preclinical evidence (14, 15). Acupoint prescriptions included GV20 (Baihui), GB8 (Shuaigu), GB20 (Fengchi), GB34 (Yanglingquan), BL15 (Xinshu), BL18 (Ganshu), BL23 (Shenshu), SP6 (Sanyinjiao), and KI3 (Taixi). The acupoint locations adhere to the National Standard of the People’s Republic of China (GB/T1236-2021) (33), as shown in Table 2 and Figure 2. Needle insertion depth ranges from 10 to 30 mm, depending on anatomical site. Needles will be retained for 30 min each session, with manual stimulation (twisting and lifting-thrusting) performed every 15 min to elicit the “deqi” sensation (such as soreness, heaviness, or distension). Treatments will be administered three times weekly for 12 consecutive weeks, totaling 36 sessions. Patients will be positioned prone with eyes covered to maintain blinding. Skin will be disinfected prior to needling. The intervention protocol follows the Standards for Reporting Interventions in Clinical Trials of Acupuncture (34). Licensed acupuncturists (with ≥5 years of experience) will receive standardized training on protocol adherence and confidentiality, with performance monitored via treatment logs.

**Table 2 tab2:** Location of acupoints.

Acupoints	Location
GV20 (Baihui)	On the head, 5 cun superior to the fronterior hairline, on the fronterior median line.
GB8 (Shuaigu)	On the head, directly superior to the auricular apex, 1.5 cun superior to the temporal hairline.
GB20 (Fengchi)	In the anterior region of the neck, inferior to the occipital bone, in the depression between the origins of the sternocleidomastoid and the trapezius muscles.
GB34 (Yanglingquan)	On the fibular aspect of the leg, in the depression anterior and distal to the head of the fibula.
BL15 (Xinshu)	On the back, below the spinous process of the 5th thoracic vertebra, 1.5 cun aside the posterior median line.
BL18 (Ganshu)	On the back, below the spinous process of the 9th thoracic vertebra, 1.5 cun aside the posterior median line.
BL23 (Shenshu)	In the lumbar region, below the spinous process of the 2nd lumbar vertebra, 1.5 cun aside the posterior median line.
SP6 (Sanyinjiao)	On the medial side of the lower leg, 3 cun above the tip of the inner ankle, at the posterior margin of the medial border of the tibia.
KI3 (Taixi)	On the posteromedial aspect of the ankle, in the depression between the prominence of the medial malleolus and the calcaneal tendon

**Figure 2 fig2:**
[figure not shown]
Location of acupoints.

#### SA group

Participants in the SA group will receive treatment with the Park sham device applied to identical acupoints to ensure participant blinding. The device uses blunt, non-penetrating needles (0.30 × 25 mm and 40 mm, Huatuo, Suzhou, China) that simulate the sensation of needling without skin penetration (see Figure 3). The system comprises transparent tubes (Φ4 × 20 mm, Φ3 × 35 mm), double-sided adhesive tape (Φ1 × 15 mm), and opaque plastic bases (Φ4 × 15 mm, Φ5 × 10 mm), manufactured by Suzhou Medical Materials Factory, batch number 240407. Patients perceive needle contact without actual skin penetration. For scalp points, the blunt needle is secured with hairpieces to enhance stability (35). Treatment frequency, duration, and practitioner interaction mirror the TA group to maintain procedural consistency.

**Figure 3 fig3:**
[figure not shown]
Park sham acupuncture device.

### Concomitant treatments

Participants who have been on stable antiparkinsonian medication regimens (dopamine agonists, levodopa, or MAO-B inhibitors, alone or in combination) for at least 3 months prior to enrollment will maintain their medication throughout the 12-week intervention and 1-year follow-up unless clinical indications necessitate adjustments (36). The use of additional antiparkinsonian or central nervous system agents is prohibited; any deviations will be documented and accounted for in statistical analysis. Medications for comorbid conditions (e.g., hypertension and diabetes) are permitted and will be documented at each visit. In case of symptom worsening, medication adjustments may be made under physician guidance, with changes recorded in CRFs and converted to levodopa equivalent daily dose (LEDD) for analysis. Stable non-acupuncture interventions (e.g., rehabilitation or exercise) unrelated to motor function are permitted; their use will be recorded at each visit and adjusted as covariates in the mixed-effects model analysis.

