#### Secondary outcomes

The secondary outcomes include change in CCMS from baseline to week 64. MDS unified Parkinson’s disease rating scale (MDS-UPDRS) (38) scores comprised Part I (non-motor aspects of daily living, range 0–52, higher scores indicate greater impairment), Part II (motor aspects of daily living, range 0–52, higher scores indicate greater impairment), Part III (motor examination), Part IV (motor complications), and total score (sum of Parts I–III, range 0–236, higher scores indicate greater impairment). Purdue Pegboard Test score (PPTS) assesses fine motor skills, with two trials averaged per session. The Timed Up and Go Test (TUG) measures the time to rise, walk 3 m, and return, with two trials averaged, and records the use of assistive devices. Six-minute walk test (6MWT) (39) measures the maximum distance walked in 6 min on a flat surface, with two trials averaged, and records the use of assistive devices, which will be conducted with researcher supervision for safety. The Non-Motor Symptoms Scale (NMSS) (15), ranging from 0 to 360, evaluates domains such as sleep/fatigue, mood, and gastrointestinal function. The 39-item Parkinson’s Disease Questionnaire (PDQ-39) (40), ranging from 0 to 100, covering 8 dimensions (e.g., mobility), measures health-related quality of life. Clinical Global Impression Scale (CGI), including CGI-S (severity) and CGI-I (improvement), will be completed by a blinded assessor. LEDD will be calculated according to the standardized conversion formula proposed by Tomlinson et al. (41), recording changes from baseline at each follow-up. All secondary outcomes will be assessed at baseline; at weeks 4, 8, and 12 (during treatment); and at weeks 38 and 64 (follow-up). Among these, the NMSS, as a key secondary outcome, will be analyzed using mixed-effects models to evaluate changes in sleep/fatigue and mood domains from baseline to month 15.

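### The mixed model adjusts for co-intervention use recorded after randomization; the covariate should be limited to its pre-randomization value

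*Protocol article*

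**What the plan says.** Under Concomitant treatments, the permitted co-interventions are described as follows: "Stable non-acupuncture interventions (e.g., rehabilitation or exercise) unrelated to motor function are permitted". The same sentence then fixes their place in the analysis: "their use will be recorded at each visit and adjusted as covariates in the mixed-effects model analysis".

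Statistical analysis describes one mixed model for primary and secondary outcomes, "with fixed effects for group, time, and group-by-time interaction, and adjusting for relevant covariates". It says of baseline variables: "Baseline covariates (e.g., age, sex, disease duration, and LEDD) will be adjusted where applicable". It also states: "Primary analyses will follow the intention-to-treat (ITT) principle, including all randomized participants".

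On medication, Concomitant treatments says of departures from the rule on additional drugs that "any deviations will be documented and accounted for in statistical analysis", and describes dose adjustments "with changes recorded in CRFs and converted to levodopa equivalent daily dose (LEDD) for analysis". Secondary outcomes lists LEDD as an outcome, "recording changes from baseline at each follow-up".

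**The concern.** An ITT comparison is protected by randomization because nothing that happens after allocation decides who is compared with whom. A covariate measured at weeks 4 to 64 does not have that protection. If acupuncture changes how much rehabilitation or exercise a patient does, adjusting for use removes the part of the effect that runs through use. If an unmeasured factor such as underlying severity drives both use and motor score, adjusting also opens a non-causal path between arm and outcome. In either case the group coefficient no longer estimates the ITT effect on CCMS.

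This is a rule that the protocol states, not a detail it leaves out. It applies to the model that yields the primary result. An analyst who follows the text could report a shifted estimate even with perfect blinding and complete follow-up.

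**Working it through.** **1. When the covariate is measured.** Table 1 has assessments at weeks 0, 4, 8, 12, 38 and 64, with randomization at week 0. Five of the six values therefore come after randomization. For the week-12 primary endpoint it is three of four (weeks 4, 8 and 12).

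**2. Whether another section limits it.** Statistical analysis gives age, sex, disease duration and LEDD as examples of baseline covariates. It then allows further relevant covariates without listing them or fixing their timing. The rule under Concomitant treatments therefore stands.

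**3. What the adjusted model estimates.** Let A be the arm (1 = true acupuncture, TA; 0 = sham, SA), C be co-intervention use after randomization, and U be unmeasured severity:

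Y = τA + βC + γU + error

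- ITT effect = τ + β × (use in TA − use in SA).
- With C in the model and no U behind it, the coefficient of A estimates τ, a direct effect.
- If U drives both C and Y, and A also affects C, the coefficient is τ plus a selection term.
- If A does not affect C, use is equal in the two arms and both quantities equal τ.

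**4. Inputs.** From Sample size calculation: difference −6.91 and SD 8.56. These are MDS-UPDRS Part III figures that the plan carries over to CCMS. They reproduce the plan's numbers:
- d = 6.91 / 8.56 = 0.81.
- A two-sample t-test needs 33.24, rounded up to 34 per group.
- 34 / 0.8 = 42.5, rounded up to 43.
- 43 × 1.2 = 51.6, rounded up to 52.

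The sample size is not affected by this point.

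The documents give no rate or effect of co-intervention use, so the rest is assumed: use in SA 50%, β = −3 points, and, where a shared cause is present, U shifting Y by 5 points per SD and also driving use. The check used a linear model with one binary covariate and 2 million simulated records per case.

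| Case | Use TA / SA | Shared cause | ITT difference | Adjusted |
|---|---|---|---|---|
| a | 50% / 50% | yes | −6.91 | −6.91 |
| b | 31% / 50% | no | −6.34 | −6.91 |
| c | 36% / 50% | yes | −6.50 | −6.12 |
| d | 24% / 50% | yes | −6.14 | −5.41 |
| e | 64% / 50% | yes | −7.32 | −7.69 |
| f | 36% / 50%, no effect of A or C on Y | yes | 0.02 | 0.80 |
| g | 24% / 50%, no effect of A or C on Y | yes | −0.01 | 1.51 |

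Hand check of case b: −6.91 + (−3) × (0.308 − 0.499) = −6.91 + 0.57 = −6.34.

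**5. Reading.** Case a shows no bias when treatment leaves use unchanged, even with a shared cause. In case d the estimate shrinks by 6.14 − 5.41 = 0.73 points (0.73 / 6.14 = 12%, or 0.73 / 8.56 = 0.09 SD). In case e it grows by 7.69 − 7.32 = 0.37 points (5%). Cases f and g give a non-zero adjusted estimate where the ITT difference is essentially zero, but only because treatment is assumed to change use without changing the outcome.

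**The case against.** The strongest reply is that the permitted co-interventions are by definition stable and unrelated to motor function. A stable co-intervention has the same value at week 12 as at baseline, so it acts as a baseline covariate, and recording it at each visit may serve only to check stability. This stands as far as it goes: if use does not change, the bias is nil. It does not rescue the wording. Stability is a condition for permission, not a guarantee over 64 weeks. If use never changed, adjusting for the visit-by-visit record would gain nothing over the baseline value. Rehabilitation and exercise can also plausibly bear on the Timed Up and Go Test, a component of CCMS.

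A second reply is that the analysis plan, which is not shown, may settle the matter. It may, but the article already states a rule, and a plan that follows it inherits the problem.

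Three stronger readings are tempting, and the documents do not support them.

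- *On-study medication is also adjusted for in the CCMS model.* A reader might infer this from "any deviations will be documented and accounted for in statistical analysis" and "with changes recorded in CRFs and converted to levodopa equivalent daily dose (LEDD) for analysis". Neither says so. Statistical analysis names LEDD among baseline covariates, and Secondary outcomes makes its change an outcome, which is reason enough to convert doses. The medication wording is not itself an error.
- *The bias is large and toward the null.* Suppose the patients with the worst change take up co-treatment (5% to 20% of the sham arm), co-treatment improves the score by 0 to 0.5 SD, and the true effect is 0.3 to 0.8 SD. Adjustment then shrinks the effect by about 7% to 30%. That describes escalation for worsening, not stable exercise. The example at 20% uptake, −0.50 to −0.36 SD, assumes that co-treatment does nothing to the score. With a looser link between uptake and outcome, shrinkage falls to about 4% or 1%. These figures illustrate a mechanism and do not estimate anything in this trial.
- *Scores after a medication change must be set to missing and imputed.* That is a separate choice of estimand and is not needed to correct this sentence.

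**Conclusion.** The point holds for the co-intervention covariate. The protocol puts rehabilitation or exercise use, recorded at visits after randomization, into the mixed model for primary and secondary outcomes. It neither limits the covariate to baseline nor marks the adjustment as supplementary. That sits badly with the declared ITT analysis.

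The bias is zero if treatment does not affect use. If use drifts differently by arm, the estimate can move either way. In the assumed settings with a true effect, the shift was between 0.37 and 0.73 points on a scale with SD 8.56. Neither direction nor size in this trial can be determined from the documents, because they give no uptake rates and no effect of the co-interventions.

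**What to change.** In Concomitant treatments, restrict the co-intervention covariate in the primary and secondary mixed models to its value before randomization. Keep recording use at every visit, and report it by arm, either descriptively or in an analysis labelled supplementary.

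For consistency, add to Statistical analysis that only baseline LEDD enters the CCMS model, as that section already suggests, and that on-study LEDD change remains an outcome. A sensitivity analysis for medication changes is optional.

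The cost is one amended sentence and one clarifying sentence. No new data, visits or participants are needed.
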